# Effects of nurse-led motivational interviewing of patients with chronic musculoskeletal pain in preparation of rehabilitation treatment (PREPARE) on societal participation, attendance level, and cost-effectiveness: study protocol for a randomized controlled trial

**DOI:** 10.1186/1745-6215-14-90

**Published:** 2013-04-02

**Keywords:** Motivational interviewing, Motivation, Adherence, Design article, Drop-outs, Working mechanism, Mediators/moderators, Societal participation

## Abstract

**Background:**

Non-adherence and drop-out are major problems in pain rehabilitation. For patients with various health problems, motivational interviewing (MI) has shown promising effects to tackle these problems. In chronic pain patients, the effectiveness of MI is however unknown. Therefore, a MI-based pre-pain rehabilitation intervention (MIP) addressing motivation, expectations, and beliefs has been developed to prepare eligible patients for rehabilitation treatment.

**Methods/design:**

Study design: A parallel randomized controlled trial including two interventions: a motivational interviewing pre-pain rehabilitation intervention (MIP) and a usual care (UC) control arm. Follow-up will be 6 months after completion of rehabilitation treatment.

Study population: One hundred and sixty (*n* = 80 per arm) patients with chronic non-specific musculoskeletal pain visiting an outpatient rehabilitation department, who are eligible to participate in an outpatient cognitive behavioral pain rehabilitation program.

Intervention: MIP consists of two sessions to prepare and motivate the patient for pain rehabilitation treatment and its bio psychosocial approach. UC consists of information and education about the etiology and the general rehabilitation approach of chronic pain. Both the MIP and UC contain two sessions of 45 to 60 minutes each.

Objective: The aim of the current study is to evaluate the effectiveness of MIP compared to UC in terms of an increase in the long-term level of societal participation and decrease of drop-out during rehabilitation treatment.

Main study endpoints: Primary outcome is the change in level of participation (according to the ICF-definition: ‘involvement in a life situation’) 6 months after completion of rehabilitation treatment. Secondary outcomes are adherence and treatment drop-out, disability, pain intensity, self-reported main complaints, (pain-specific) self-efficacy, motivation, and quality of life. Costs are calculated including the costs of the pre-treatment intervention, productivity losses, and healthcare utilization. Potential moderators and active ingredients of MI are explored. For the process evaluation, parameters such as MI fidelity, feasibility, and experiences are explored.

**Discussion:**

The results of this study will provide evidence on the effectiveness of this MI-based pre-treatment in pain rehabilitation. Furthermore, a cost-effectiveness analysis and exploration of moderating and working mechanisms of MI and an extensive process evaluation takes place.

**Trial registration:**

Nederlands trial register NTR3065

## Background

Chronic non-specific musculoskeletal pain is a major health burden. It occurs in approximately 10% of the general population [1] and causes disability [2], medical expenses [3], and a high amount of work absenteeism [4].

In the Netherlands, cognitive behavioral therapy (CBT)-based approaches are part of usual rehabilitation care for patients with non-specific chronic pain [5], and also recommended in the Dutch guidelines [6]. The common assumption of CBT in rehabilitation is that pain and disability are not only influenced by biomedical factors but also by psychological and social factors, which is referred to as the bio psychosocial approach [7]. The primary aim of rehabilitation treatment is to increase the patient’s ability to cope with pain instead of curing pain. The ultimate intention is to increase the patient’s level of participation in society and his/her quality of life [8]. The ultimate goal and key outcome of rehabilitation is therefore societal participation. According to the International Classification of Functioning, Disability and Health (ICF), participation is therein defined as ‘involvement in a life situation’ whereas the opposite, participation restrictions, are defined as ‘problems an individual may experience in involvement in life situations’ [9].

The Initiative on Methods, Measurements, and Pain Assessment in Clinical Trials (IMMPACT) does not mention the measurement of participation [10]. But in the field of rehabilitation, participation is seen as an important concept in order to reflect meaningful patient-centered outcomes [11]. It is suggested that those outcomes should be included more often in trials [12].

Reviews have shown a moderate effectiveness of cognitive behavioral treatments in chronic non-specific musculoskeletal pain [13] and low back pain [14]. Behavioral therapy is more effective than usual care in terms of pain relief [15], and similar effects are shown for functioning after an intensive multidisciplinary bio-psycho-social rehabilitation program [16].

Unfortunately, in the current rehabilitation care, non-adherence and drop-out are major problems. Adherence rates are low in patients with chronic conditions [17], and subsequently, drop-out of pain rehabilitation programmes, ranging from 9% to 42%, is high [18-20]. Previous research showed that adherence and non-drop-out of treatment is related to a better outcome in physical and emotional functioning and pain severity [21]. Adherence is influenced by multiple factors such as the healthcare provider-patient relationship, the patient’s self-efficacy to be able to make changes [22], and the patient’s satisfaction with improvement [23].

In order to improve adherence and motivation to prevent drop-out, and to strengthen self-efficacy, motivational interviewing (MI) has been proposed [24]. Miller and Rollnick, the founders of MI, defined it as ‘directive, client-centred counselling style for eliciting behaviour change by helping clients to explore and resolve ambivalence’ [25]. The overall goal is to increase the client’s intrinsic motivation to change and enhance behavioral change [26]. MI was originally developed for problem drinkers [27] and in the beginning applied in the addiction field only (for example, [28,29]). Meta-analyses showed that using MI as a pre-treatment yielded the best outcomes compared with other active treatments [30-32]. Therein, MI was designed to prepare clients for further treatment such as CBT or an inpatient program. Furthermore, the effective application ranged from a variety of disorders such as addiction (except smoking cessation), increasing healthy behaviors, and the management of chronic illnesses. MI as treatment approach is fairly new in the field of chronic pain. MI has been applied with promising results in two small randomized controlled trials (RCTs) within primary care for patients with chronic pain conditions. Habib *et al*. [33] found significant increases in attending self-management workshops after a psychologist-led two-session MI-based feedback interview compared with an attention placebo interview [33]. Another recent study found a MI-adapted intervention added to outpatient physiotherapy for patients with back pain effective in enhancing motivation and exercise adherence compared to physiotherapy alone [34].

With the results of these studies in mind, it is seems promising to explore the effects of MI on non-adherence and drop-out in chronic pain rehabilitation care, and participation afterwards, where patients are characterized by a high levels of disability and complex problems.

### Aims

The primary objective of this current project is to study the effectiveness of MI by means of the MIP intervention. The interventions aims at decreasing drop-out rate and increasing adherence to treatment program to reach a high level of societal participation ultimately in patients with non-specific musculoskeletal chronic pain, who have been selected for pain rehabilitation treatment.

The main research questions are:

1. What is the effectiveness of MI-based pre-treatment (MIP) compared to usual care (UC) on the level of participation, treatment drop-out rate, and adherence in patients with chronic non-specific musculoskeletal pain following pain rehabilitation?

2. What is the cost-effectiveness and cost-utility of MIP, compared to UC from a societal perspective?

3. What is the feasibility of the MIP intervention in terms of MI fidelity (process evaluation)?

4. What are experiences of nurses and patients in terms of satisfaction with and barriers of the MIP intervention (process evaluation)?

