### Hypotheses

1a. It is expected that patients’ level of social participation will be higher in the MIP intervention condition compared to the UC after pain rehabilitation treatment and at 6-month follow-up after finishing the rehabilitation treatment.

1b. It is hypothesized that drop-out rates will be lower and adherence to the treatment and the level performing daily activities) will be higher in the MIP condition compared to the UC.

2. It is hypothesized that MIP will be more efficient compared to UC, both in effects as well as utilities.

3. It is hypothesized that the MIP intervention is feasible for the participating nurses and the MI fidelity of the MIP intervention is sufficient.

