### Sample size

The sample size calculation is based upon an estimated difference in change in level of participation between baseline and 6-month follow-up (after completion of the rehabilitation treatment) as assessed by the Utrecht Scale for Evaluation of Rehabilitation-Participation (USER-P) [35,36]. Reproducibility [37], responsiveness [38], and validity [37] of the USER-P are satisfactory. As participation is the important outcome in rehabilitation, we have chosen this as primary outcome. The scale consists of the three aspects of participation represented by the subscales Frequency, Restriction, and Satisfaction. The sum score of each subscale is converted to scores on a scale ranging from 0 to 100. There is no USER-P total score.

Our sample-size calculation is based upon the subscale Satisfaction. This subscale is the most important part of participation as it marks the subjective experience of participation [9]; therefore we have chosen this one.

As at this moment no information is available about the USER-P in a pain population regarding normative values, clinically relevant change, and clinically relevant difference, our study is exploratory of character. In a study by van der Zee (2011) the USER-P is taken in different patient groups at three different points in time [38]. As these groups were part of a cohort study, nothing is known about differences after a specific treatment. We know from other studies that multidisciplinary pain rehabilitation treatment is moderately effective with effect sizes ranging from 0.30 for behavioral outcomes up to 0.40 for functional outcomes [14]. We expect an additional effect for the MIP intervention since systematic reviews of motivational interviewing-based interventions show an effect size ranging from 0.27 up to 0.40 when compared with a weak comparison group [30-32,39]. It has to be said that in those reviews no study in the field of chronic pain or rehabilitation treatment was taken into account. Therefore, our power calculation is based on the following two assumptions:

1. Using an expected mean change of 5 points within UC is expected whereas a difference of additional 5 points (thus at least 10 points in total) within MIP in the USER-P sub scale Satisfaction is considered as clinically relevant. Those numbers are estimates as the clinically relevant difference is not known yet.

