2. Assuming a standard deviation of 10 points in both groups, the standardized effect size, Cohen’s d, is (10–5)/10 = 0.5 indicating a medium additional effect size of the MIP [40].

Assuming power (1-β) of 80%, α = 0.05, two-sided testing, and holding the above mentioned assumptions, would necessitate *n* = 128 participants (*n* = 64 per arm). With an expected total drop-out of 20% (10% drop-out from the study, another 10% drop-out during the usual rehabilitation treatment as our unsystematic registration has shown), *n* = 160 (*n* = 80 per arm) was chosen as the optimal total sample size. Additionally, as the recruitment of 160 participants in the region of South-Limburg/the Netherlands is feasible in a time range of 18 months, we have chosen for this amount of participants.

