#### Effect evaluation

Baseline data will be analyzed to describe the characteristics of all participants and to check for significant imbalances between the two groups. Possible baseline differences between the intervention group and the control group will be tested by an independent samples *t*-test (normal distribution) or Mann–Whitney U tests (non-normal distribution) in the case of continuous variables. In the case of dichotomous variables, a Chi-square test will be used. In case of imbalances in prognostic factors between both randomized groups, an adjustment for those factors will take place. The number of drop-outs and follow-up losses in both groups will be reported based on descriptive data. Differences in primary and secondary outcome measures between MIP and UC will be analyzed using repeated measurements techniques and multilevel analysis. This approach is chosen because repeated measures within individual subjects are taken. A *P* value <0.05 is considered statistically significant. Data will be analyzed according to the intention-to-treat principle. All outcomes will be assessed at each follow-up moment by taking into account a specific a priori hypothesis. Additionally, per protocol analyses will be performed to assess whether protocol deviations have caused bias.

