### Moderation analysis

As secondary analyses, the working mechanisms of MI are investigated. For testing moderation, an interaction term of the potential moderator is constructed and analyzed by linear regression.

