### Process evaluation

Results of the questionnaires for the process evaluation of participants and nurses will be analyzed descriptively. A summary score of MI fidelity will be computed by ratings of the MI-consistent behavior evaluated by the MITI. Summary score thresholds are known for beginning proficiency level and competency level [94]. A binary variable MI fidelity will be computed and used in analyses for the effectiveness of MI as well as working mechanisms of MI. MI fidelity is furthermore used in mediation analyses as hypothesized mediator in the path between the MI intervention and its effect.

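### The Aims route MIP's benefit through drop-out and adherence, but the planned mechanism analyses cover only moderators and MI fidelity, so the adherence-to-participation link goes untested

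*Protocol article*

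**What the plan says.** The Aims set out a chain: "The interventions aims at decreasing drop-out rate and increasing adherence to treatment program to reach a high level of societal participation ultimately". The Background supports both links. It proposes MI as a means to better adherence, and it cites research relating adherence and completion to better outcome.

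The questions and analyses then treat the elements of the chain separately:

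- Research question 1 (Aims) lists them side by side: "What is the effectiveness of MI-based pre-treatment (MIP) compared to usual care (UC) on the level of participation, treatment drop-out rate, and adherence".
- Hypothesis 1b begins "It is hypothesized that drop-out rates will be lower and adherence to the treatment" and goes on to expect a higher level under MIP, which is a comparison between arms.
- Effect evaluation: "Differences in primary and secondary outcome measures between MIP and UC will be analyzed using repeated measurements techniques and multilevel analysis".
- Moderation analysis: "As secondary analyses, the working mechanisms of MI are investigated. For testing moderation, an interaction term of the potential moderator is constructed", to be analysed by linear regression.
- Process evaluation, under Statistical analysis: "MI fidelity is furthermore used in mediation analyses as hypothesized mediator in the path between the MI intervention and its effect".

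The Discussion part of the abstract and the closing paragraph of the article both say the trial will inform on working mechanisms. Drop-out and attendance come from the patient registry (Data collection; Secondary outcomes), and Table 2 lists them only as secondary outcomes.

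**The concern.** An arm-by-moderator interaction asks whether the effect of MIP differs between kinds of patient. It does not show whether the effect passes through attendance. MI fidelity describes how the nurse delivered the pre-treatment session. It is not patient behaviour during rehabilitation and is not a step in the chain that the Aims describe. This goes beyond detail left to another document: the article does specify mechanism analyses and does choose a mediator, and neither covers its own stated path.

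At stake is the interpretation of a benefit. If participation at T4 is better under MIP and attendance is also better, readers will be inclined to join the two, and nothing planned would support or contradict that.

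**Working it through.** **1. The plan's own figures.** From Sample size: difference 10 − 5 = 5 points, SD 10, so d = 0.5; two-sided α = 0.05, power 80%. The t-test calculation gives 63.8, hence 64 per arm and 128 in total; 128/(1 − 0.20) = 160. Both figures reproduce. No stated number is wrong on this point.

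**2. Links against planned analyses.**

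- MIP to drop-out and adherence: compared by arm (Effect evaluation). Tested, with randomisation.
- Drop-out and adherence to participation: no analysis.
- Indirect effect of MIP through adherence: no analysis.
- MIP to participation: primary comparison. Tested, with randomisation.
- Moderator interactions: for whom, not through what.
- MI fidelity: delivery of the session. Of 80 × 2 = 160 planned MIP sessions, 20% are scored, about 32.

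**3. How much could completion alone carry?** Inputs: "Using an expected mean change of 5 points within UC is expected", an assumed extra 5 points under MIP, and "another 10% drop-out during the usual rehabilitation treatment as our unsystematic registration has shown". The Background cites drop-out of 9% to 42%. Assume that drop-outs gain nothing and that MIP removes all drop-out. The article does not say whether the 5-point usual-care (UC) gain includes drop-outs, so both readings are shown, with d now the drop-out proportion.

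- Reading A, 5 points is the mean over all UC patients. Extra gain = 5/(1 − d) − 5: 0.49 at 9%, 0.56 at 10%, 3.62 at 42%.
- Reading B, 5 points is the mean among completers. Extra gain = 5 − 5(1 − d) = 5d: 0.45 at 9%, 0.50 at 10%, 2.10 at 42%.

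As a share of the assumed 5 points, that is 10% to 11% at the protocol's 10% rate, and 42% to 72% at the highest cited rate. Put the other way, for drop-out alone to yield 5 points at a 10% rate, each averted drop-out would have to be worth 5/0.10 = 50 points on a 0–100 scale. Most of the assumed effect would therefore have to come by another route, such as attendance among completers or a direct effect.

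**4. Strength of the planned first-link test for drop-out.** Take 80 per arm and a halving from 10% to 5%. Null SE = √(2 × 0.075 × 0.925/80) = 0.0416; alternative SE = √((0.09 + 0.0475)/80) = 0.0415. Then z = (0.05 − 1.96 × 0.0416)/0.0415 ≈ −0.76, so power is about 22%; 435 per arm would be needed for 80%. For 42% to 21%, power at 80 per arm is 82%.

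**5. What a mediation analysis could show.** Analysable numbers are 160 × 0.80 = 128 to 160 × 0.90 = 144.

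- Second link only, Fisher z, assumed partial correlation 0.25 or 0.30 between attendance and T4 participation: power 81% or 93% at n = 128, and 86% or 96% at n = 144.
- Both links jointly significant, by simulation (4,000 trials per setting, 64 per arm, second-link coefficient 0.30). If MIP shifts attendance by 0.27 SD, the indirect effect is 0.27 × 0.30 × 10 = 0.8 points and power is 30%. At 0.40 SD it is 1.2 points and 57%. The values 0.27 and 0.40 are the ends of the MI effect-size range quoted in Sample size; applying them to attendance, like the correlations, is an assumption.

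**6. Definition of the mediator.** Secondary outcomes defines pre-treatment adherence as attended over planned sessions, but rehabilitation adherence as scheduled over attended. On the second formula a patient attending half the sessions scores 2, one attending all scores 1, and one attending none has no value.

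**The case against.** The strongest reply is that the sentence in the Aims is rationale. No numbered research question or hypothesis asks for mediation, and each stated question gets an intention-to-treat comparison that is valid whatever the path. This stands: the primary result, the sample size and the secondary comparisons are untouched.

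A reader might infer that a null result would be equally uninterpretable. The documents do not support that. Drop-out and adherence are compared by arm, so the first link is tested. A difference there with no difference in participation would point to the second link, and clear evidence of no difference there would count against the path. The qualification is the low power for drop-out if the UC rate is near 10%.

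A reader might also infer that the article breaks a promise about adherence specifically. It does not list adherence among its working mechanisms; the section on active ingredients names stage of change and MI integrity. What can be said is narrower: mechanism insight is promised in general, the Moderation analysis section offers a method that cannot give it, and the path in the Aims is left out.

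Lastly, the statistical analysis plan is not shown and could add mediators. That is possible, and it is one reason to treat this as a modest point.

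**Conclusion.** The point holds in a limited form. The article states a path through drop-out and adherence, labels moderator interactions as an investigation of working mechanisms, and names one mediator that is not on the path. The second link and the indirect effect are untested, so mainly a positive T4 result could not be credited to better adherence.

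The size is illustrative: completion alone could account for about a tenth of the assumed 5 points at 10% drop-out, and for 42% to 72% at a 42% rate. These figures rest on zero gain in drop-outs, complete removal of drop-out, and the 5-point UC gain carried over to each rate. They show that attribution to completion cannot be taken for granted; they do not show an error in the plan. The 81% to 96% power covers the second link only and should not be read as power for the indirect effect, which is lower. The analysis is worth adding as exploratory, not confirmatory.

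**What to change.** - In Secondary outcomes, define rehabilitation adherence as attended divided by scheduled sessions, matching the pre-treatment formula, and say how patients who never start rehabilitation are scored.
- In Moderation analysis, keep interaction terms for moderation only and drop the suggestion that they examine mechanisms.
- There and in the statistical Process evaluation section, add one exploratory mediation analysis: arm, then rehabilitation attendance, then USER-P Satisfaction at T4. Adjust for baseline USER-P, hospital and the baseline attrition risk factors listed under Demographic and medical variables. Report indirect and direct effects with bootstrap 95% intervals.
- Use completion as a second mediator only where T4 data exist for patients who left rehabilitation. Sample size counts them as losses (10% of 160 = 16 patients); if none has T4 data, completion does not vary among those analysed.
- State the no-unmeasured-confounding assumption, and make no claim that MIP works through adherence unless the indirect effect supports it.

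The cost is a few sentences and one secondary analysis on data already collected, with no change to the sample size. The downside is that the mediator is not randomised, the interval will be wide, and power for the completion path is low if UC drop-out is near 10%.
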